#### 4.4 Sample size calculation

The sample size for this RCT was computed using software package PASS 11. The sample size calculation is based on the study performed by Saliba (Saliba 2015), in which complete control of vertigo was reached in 96,5% of the patients who underwent EDB. According to literature, endolymphatic sac decompression is effective in  $\pm 70\%$  of the patients (Brinson 2007, Convert 2006, Durland 2006).

We compare MD participants undergoing an operation with clip (EDB group: A group) independently with MD participants undergoing operation without clip (decompression group: B group). Null hypothesis is that the percentage points difference between groups is nil ( $p_A = p_B$ ), with two-sided alternative hypothesis ( $p_A \neq p_B$ ) and with anticipated 25% percent difference ( $p_A = 95\%$  and  $p_B = 70\%$ ). Power is at least 80%. The chance of a false positive finding for either of the analyses is controlled at the 5% level (family wise error rate). To obtain a power of at least 80% for Fisher's Exact test, the required sample size is 32 in groups A and B (allocation ratio = 1). Loss to follow-up will likely occur in a small percentage of cases ( $n=5$  per arm). No selective loss to follow-up is anticipated and a missing-at-random assumption seems reasonable. Missing outcomes will therefore be imputed using multiple imputation in the main analysis. Two sensitivity analyses will be conducted as well, where missing outcomes will be treated as failures or success, respectively. In this case the sample size would be 37 in group A and B (allocation ratio = 1). The total number of participants would be 74.

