#### **8.5 Replacement of individual subjects after withdrawal**

The number of participants (as mentioned in chapter 3) takes into account that at least 15% of the participants in both arms of the study will drop out. We therefore do not expect to replace participants.

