#### **8.6 Follow-up of subjects withdrawn from treatment**

A participant may be excluded from the study prior to the expected protocol completion for safety reasons, failure of subject to adhere to protocol requirements, or subject consent withdrawal. Since early withdrawal could be related to the surgery, it is of great importance to analyse these final data for the integrity of the study. If a participant withdraws consent to continue follow up participation, attempts should be made to obtain permission to record at least primary outcome data. The participant will be contacted by phone and email, the next-of-kin will be contacted, a letter asking to contact us will be send or the patient's general practitioner will be contacted.

If a participants withdraws its consent, he/she is allowed to do so without further explanation. If this is the case, participants should contact the ENT-surgeon who takes care of follow up. This ENT-surgeon then contacts the coordinating researcher. The data that were collected until the moment of consent withdrawal, will be used in the analyses.

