#### 10.1.1 Imputation of App-recorded data

The daily questionnaire taken via the DizzyQuest app is likely to contain missing data. All other missing data will be labelled 'NAmissing' in SPSS. Multiple imputation will be used to create complete data sets. Depending on the missing data pattern different strategies will be followed.

Imputation variables are base line measurements, time-course measurements and daily App-data.

- Missingness  $\leq 10\%$

If little data is missing, the data will be treated as one data-row per patient (wide format).

In this case, information for imputing missing values will be taken from the exact same time points of other patients. This strategy can account for possible time trends.

- Missingness  $> 10\%, \leq 50\%$

If more data is missing, the data of each patient will be split into one row per day (long format), when the previous 10 days will be included in each row. After imputation, the previous days will be removed to avoid duplication of data. This strategy includes information on missing data across time periods and can lead to wrong imputations for time trends longer than 10 days.

- Missingness  $> 50\%$

The same strategy as for missingness between 10% and 50% is followed except for including a smaller time window. 10 previous days will be used. If all primary outcome data are not available (missing), the participant will be excluded from the analyses. The a priori sample size estimation has been corrected for this.

The above cut-offs and time ranges reflect expectations. Actual values will be selected based on the variability of imputed values.

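### With equal losses per arm, the two pre-stated missing-outcome sensitivity analyses give the same risk difference, so they cannot show its sensitivity to loss whose outcome differs by arm

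*Protocol*

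**What the plan says.** Protocol 4.4 allows for 5 losses per arm, raising 32 evaluable participants per arm to 37 randomised. On the mechanism of loss it says "No selective loss to follow-up is anticipated and a missing-at-random assumption seems reasonable". From this it concludes: "Missing outcomes will therefore be imputed using multiple imputation in the main analysis". It then adds: "Two sensitivity analyses will be conducted as well, where missing outcomes will be treated as failures or success, respectively". The last word separates the two analyses, not the two arms, so each analysis applies one rule to everybody.

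Protocol 8.6 takes a more cautious view of why people leave: "Since early withdrawal could be related to the surgery". Section 8.5 expects that "at least 15% of the participants in both arms of the study will drop out", which is slightly more than the 4.4 allowance. Section 10.1 names a chi-square test, or Fisher's exact test, for the primary outcome. Sections 10.1.1 and 10.1.2 deal with gaps in the app data. Neither they nor any other section of the protocol states an analysis in which the missing are treated differently by arm.

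**The concern.** The estimate of a two-arm comparison is most vulnerable when the people lost from one arm did worse than the people lost from the other. A rule that gives every missing participant the same outcome moves both arms together. With equal numbers lost, it adds the same count to both numerators, or nothing to either, and the difference between arms is the same under both rules.

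At stake is how the result is described. Two checks that agree exactly on the risk difference look like evidence of robustness, but with equal losses the agreement is arithmetic and would appear for any data. A conclusion that depends on the missing-at-random assumption could be reported as having survived its checks. Section 3 says the results go to the national body that decides on implementation, so the wording matters.

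**Working it through.** **Inputs.** From 4.4: success rates 95% (EDB) and 70% (decompression), 32 evaluable per arm, 5 lost per arm, 37 randomised per arm. From 10.1: two-sided tests at 5%, chi-square or Fisher.

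**The plan's own figure.** 32 + 5 = 37 per arm and 2 × 37 = 74 in total, which reproduces. The allowance is 5/37 = 13.5%. The 15% in 8.5 would be 0.15 × 37 = 5.6 per arm.

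**Illustrative counts (assumption).** 0.95 × 32 = 30.4 and 0.70 × 32 = 22.4, rounded to 30/32 and 22/32. The observed difference is 93.75% − 68.75% = 25.0 points (Fisher p = 0.022, uncorrected chi-square p = 0.010). This stands in for the multiple-imputation result, which cannot be computed without data.

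**Algebra.** Let s_A and s_B be the observed successes, m the number lost in each arm, and k = 0 (missing = failure) or k = 1 (missing = success). Then

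RD = (s_A + k·m)/37 − (s_B + k·m)/37 = (s_A − s_B)/37.

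The term k·m cancels for any m that is equal in both arms. Both checks therefore equal the observed difference multiplied by 32/37, here 25.0 × 32/37 = 21.6 points.

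**Results with 5 lost per arm.**

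| Treatment of the missing | EDB | Decompression | RD (points) | Fisher p | Chi-square p (uncorrected) |
|---|---|---|---|---|---|
| All failure (stated in 4.4) | 30/37 | 22/37 | 21.6 | 0.074 | 0.042 |
| All success (stated in 4.4) | 35/37 | 27/37 | 21.6 | 0.024 | 0.012 |
| EDB failure, decompression success (not stated) | 30/37 | 27/37 | 8.1 | 0.58 | 0.41 |
| EDB success, decompression failure (not stated) | 35/37 | 22/37 | 35.1 | 0.0006 | 0.0003 |

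The stated pair spans 0 points. The extremes span 35.1 − 8.1 = 27.0 points.

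**All allocations.** Let a and b be the successes among the 5 missing in the EDB and decompression arms, each from 0 to 5. That gives 6 × 6 = 36 tables of (30 + a)/37 v (22 + b)/37. With Fisher's test 18 of 36 have p > 0.05. With the uncorrected chi-square test 13 of 36 do, although both stated checks are below 0.05 on that test. The 36 tables are not equally likely, so these counts are not probabilities.

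**Unequal losses.** With 3 lost in EDB and 7 in decompression (32/34 v 21/30 observed): all failure gives 32/37 − 21/37 = 29.7 points, all success 35/37 − 28/37 = 18.9 points. With 7 and 3 lost (28/30 v 24/34 observed): all failure gives 28/37 − 24/37 = 10.8 points, all success 35/37 − 27/37 = 21.6 points. The identity then no longer holds.

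**The case against.** The strongest reply is that the pair is more informative than the identity suggests. A sensitivity analysis is read against the main analysis as well as against its partner. Against the stand-in main result (25.0 points, Fisher p = 0.022), treating all missing as failures gives 21.6 points and p = 0.074. That check would not look reassuring, and it does test non-random loss in the same direction in both arms. Section 10.1 names a test and no risk-difference estimator, and on Fisher's test the two checks fall on either side of 0.05. Five per arm is also a planning allowance, not a forecast of equal counts. All of this stands, and it limits the point to the risk difference under equal losses.

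A reader might infer from 8.6 that loss is expected to differ by arm. The text does not say so: it links withdrawal to surgery, which every participant has, and not to allocation. Patients and the follow-up surgeon are blinded (8.2.2), the arms share the same surgical exposure up to the closing of the clip, and 8.6 provides for efforts to obtain primary outcome data after withdrawal. These features make the arm-opposed extremes less plausible. They do not rule out milder differences between arms.

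Finally, tipping-point tables are often left to a statistical analysis plan, and one may exist. That would matter if the protocol were silent. Here 4.4 fixes a particular pair, and the choice of that pair is what is questioned.

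**Conclusion.** The point holds in limited form. With the planned equal losses, the two checks in 4.4 return one and the same risk difference, whatever the data. They cannot show whether that difference is sensitive to loss whose outcome differs by arm. In the illustration, the untested region runs from 8.1 to 35.1 points and includes allocations that lose significance on either test named in 10.1.

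A reader might go further and infer that the checks cannot detect selective loss at all, or would look reassuring whatever its mechanism. The protocol does not support that: the p-values differ, same-direction loss is tested against the main analysis, and unequal losses separate the two estimates.

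The identity is algebraic and needs only equal losses. The sizes rest on the assumed counts of 30/32 and 22/32, on 5 lost per arm, and on observed data standing in for multiple imputation. This is a cheap improvement, not a fault that invalidates the analysis.

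**What to change.** In 4.4, keep multiple imputation as the main analysis and keep the existing pair. Add a tipping-point table over every number of successes among the missing in each arm, with the risk difference and the primary-test p-value in each cell, and mark where p crosses 0.05. The corners of the table are the two stated checks and the two arm-opposed cases. State beforehand that the arm-opposed corners are bounds and not likely scenarios, and name the test used in the table, since chi-square and Fisher place the boundary differently.

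While editing, reconcile 4.4 with 10.1.1, which says: "If all primary outcome data are not available (missing), the participant will be excluded from the analyses". The table needs those participants in the denominator.

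The cost is a few lines of text and a short program, with no new data or participants. The downside is a little extra analysis and an unfavourable extreme cell that will need explanation. The change should be made before unblinding.

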#### 4.5 Numbers needed to treat

The number needed to treat (NNT) is an epidemiological measure used in communicating the effectiveness of a health-care intervention. The NNT is the average number of patients who need to be treated to prevent one additional bad outcome (e.g. the number of patients that need to be treated for one of them to benefit compared with a control in a clinical trial). For this study: NNT A vs B:  $100/(p1-p2) = 100/(95\%-70\%) = 100/25 = 4$

## 5. TREATMENT OF SUBJECTS

Participants in both arms of this study will undergo surgery. Both surgical procedures are described below.

### 5.1 Investigational treatment

The first part of the surgical procedure is equal in the two groups. First, a canal wall-up mastoidectomy is performed: the mastoid tegmen, sigmoid sinus, and sinodural angle are identified, and the posterior bony external ear canal wall is thinned. The posterior semi-circular canal (PSCC) and the dura mater of the posterior fossa are identified. Using the prominence of the horizontal semi-circular canal, Donaldson's line is identified to approximate the position of the endolymphatic sac. The bone over the sac and the dura are thinned with diamond burrs. The sac is completely skeletonized. The infralabyrinthine dura is exposed because the main body of the sac and its lumen often lie within this area. The bone of the vestibular aqueduct operculum is dissected. The posterior fossa dura from the retrolabyrinthine bone medial to the sac around the endolymphatic duct is exposed in order to identify the duct in its superior and inferior part in continuity from the endolymphatic sac, and to create a place to insert the tips of the instrument to clip the duct. At this level, care must be taken not to traumatize the dura, which is often thin. An (open) clip is then placed around the endolymphatic duct. After this placement, but before randomisation, a CT-scan of the petrous bone is performed to assess if the clip is adequately placed around the endolymphatic duct. If the duct is identified correctly and the clip is adequately placed, randomisation takes place.

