### **Secondary objectives**

We will determine whether EDB surgery compared to a decompression operation during the 1-year follow up period has a beneficial effect on:

- Cumulative incidence of vertigo bouts
- Hearing
- Use of escape medication (including intratympanic injections)
- Co-interventions (ablative procedure)
- Complications of surgery
- FLS
- DHI
- THI
- SF-36
- EQ-5D VAS
- CEA
- iPCQ
- iMCQ
- BIA
- Endolymphatic hydrops and perilymph signal intensity on MRI
- Physiotherapeutical outcomes: balance, gait, visual acuity

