#### - Surgical procedure in EDB group

If the patient is allocated to the EDB-group, the clip is closed. The size and numbers of clips used will be determined intraoperatively (Weck Horizon, size 'micro' to 'wide, Teleflex). The titanium clips are applied by using a clip applicator (Weck Horizon) and a McGee bending forceps (Aesculap).

Theoretically, it is possible that the endolymphatic duct cannot be identified. In that case, the endolymphatic sac is separated from the posterior canal to ensure an arrest of the flow of endolymphatic fluid between the inner ear structures and the endolymphatic sac. This is done by placing a barrier of autologous temporal fascia glued with Tisseel. This way, the same result as blockage with a clip is obtained.

In the case of tearing of the dura leading to liquor leakage, this will be treated with tisseel, fascie and novacol. The cortex is not restored. The skin is closed in a regular way.

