### **9.2 AEs, SAEs and SUSARs**

#### **9.2.1 Adverse events (AEs)**

Adverse events are defined as any undesirable experience occurring to a patient during the study, whether or not considered related to the performed (EDB/endolymphatic sac decompression) surgery. All adverse events reported spontaneously by the patient or observed by the investigator or her staff will be recorded.

As with every surgical procedure, the operation that patients undergo comes with risks. Data in a systematic review and meta-analysis regarding perioperative and anaesthetic related mortality suggest a mortality of 34 per million (Bainbridge, 2012).

The specific risks of this surgical procedure are:

- Injury to the facial nerve: according to Saliba's protocol (2015) this occurs in less than 1% of the patients.
- Injury to posterior semi-circular canal with loss of vestibular function
- Injury to the sigmoid sinus
- Hearing loss: in less than 4% of the patients, permanent hearing loss of the operated ear was reported (Saliba, protocol 2015).
- Leakage of cerebrospinal fluid (CSF). Minor leakage occurred in 10-15 %. This was solved intraoperatively by filling with muscle autograft temporalis fascia with biological glue. There

were no postoperative complications due to the leakage (Saliba's protocol 2015; Asmar 2016). It is important to note that the surgery procedure was optimized by [name]. We expect that this results in a lower rate of CSF leaks. [name] follows the dura of the posterior cranial fossa, and has good vision at the horizontal semicircular canal after visualising Donaldson's line.

- Meningitis

- According to the study performed by Saliba, 11 out of 57 patients experienced a post-operative benign paroxysmal positional vertigo (BPPV) (Saliba, 2015). In the pilot group of 66 patients operated by [name], BPPV was not reported. The difference in BPPV incidence may be due to the enhanced technique; Saliba works towards the posterior canal whilst [name] follows the dura of the posterior fossa and usual does not blue line the posterior canal.

Adverse effects due to natural course of MD are:

- worsening of hearing loss
- worsening of vertigo
- occurrence of bilateral MD
- worsening of tinnitus

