## 10. STATISTICAL ANALYSIS

Statistical Data analysis of the study data will be performed using SPSS (version 17.0). All analyses will be performed through Intention to treat.

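### Complications of surgery are compared by arm, and expected to favour EDB, without separating events before and after the intraoperative randomisation

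*Protocol*

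**What the plan says.** Section 5.1 describes one operation up to the point of allocation: "The first part of the surgical procedure is equal in the two groups". That shared part covers the mastoidectomy, skeletonising the sac, exposing the dura and the duct, placing an open clip and a CT scan. The protocol itself locates a hazard there: "At this level, care must be taken not to traumatize the dura, which is often thin". Allocation follows: "If the duct is identified correctly and the clip is adequately placed, randomisation takes place". The arms then part: "If the patient is allocated to the EDB-group, the clip is closed".

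The secondary objectives in section 2 open with "We will determine whether EDB surgery compared to a decompression operation during the 1-year follow up period has a beneficial effect on", and the list includes "Complications of surgery". The end of section 1 hypothesises that these outcomes will be better after EDB. Section 8.1.2 names the outcome without a definition or a starting point for counting. Section 10.2.2 sends all secondary outcomes to a linear mixed model by arm. Section 10 adds "All analyses will be performed through Intention to treat".

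On background risk, section 9.2.1 reports for cerebrospinal fluid leakage in earlier experience: "Minor leakage occurred in 10-15 %. This was solved intraoperatively".

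**The concern.** Allocation can only affect what happens after it. A dural tear, sinus injury or canal injury recognised before the randomisation call is baseline information, yet as written the by-arm comparison can include it. Each such event adds the same expected background to both arms, which makes any difference caused by the allocated step harder to see.

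The direction of the hypothesis adds to this. On the description in section 5.1, EDB is essentially the shared operation plus closing the clip. Fewer surgical complications is then hard to justify as the expected result; the question the design can answer is whether the added step causes harm. A null comparison of all complications could be taken as reassurance about the clip when part of what was compared could not have differed by allocation.

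Timing relative to allocation is also hard to reconstruct later, so it has to be recorded during the operation.

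**Working it through.** The protocol gives no figure for a between-arm difference in complications, so there is none to reproduce. The calculation below is an illustration.

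**Inputs**
- Patients: 37 per arm, 74 in total (section 4.4).
- Share of patients with an event before allocation, q: 10% and 15%. This borrows the minor leakage rate in section 9.2.1. That all such leaks precede allocation is an assumption.
- Post-allocation risks, a for EDB and c for decompression: assumptions, since the protocol gives none by arm.
- Test: two-sided Fisher's exact at 5%, used because a patient either has an event or not. Section 10.2.2 names a linear mixed model instead.

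**Number of pre-allocation events.** Expected count is 74 × 0.10 = 7.4 to 74 × 0.15 = 11.1. The difference in counts between arms has mean zero and SD √(74·q·(1−q)), which is 2.6 for q = 10% and 3.1 for q = 15%. So there is noise, but no expected advantage to either arm.

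**Dilution.** Treating the two stages as independent, the risk of any event is 1 − (1−q)(1−a) for EDB and 1 − (1−q)(1−c) for decompression. Their difference is (1−q)(a−c), so the risk difference shrinks by exactly q.

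With a = 20% and c = 5%:
- q = 10%: EDB 1 − 0.90 × 0.80 = 28.0%; decompression 1 − 0.90 × 0.95 = 14.5%.
- q = 15%: EDB 1 − 0.85 × 0.80 = 32.0%; decompression 1 − 0.85 × 0.95 = 19.25%.

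The standard error (SE) is √[(p₁(1−p₁) + p₀(1−p₀))/37]. For post-allocation events only it is √[(0.1600 + 0.0475)/37] = 7.5 points.

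| Events counted | Risks | Relative risk | Risk difference | SE | Fisher power |
|---|---|---|---|---|---|
| After allocation only | 20% vs 5% | 4.0 | 15.0 points | 7.5 points | 36% |
| All, q = 10% | 28.0% vs 14.5% | 1.93 | 13.5 points | 9.4 points | 21% |
| All, q = 15% | 32.0% vs 19.25% | 1.66 | 12.8 points | 10.0 points | 17% |

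**Sensitivity to the assumed risks.** Power for post-allocation events only, then for all events at q = 10% and q = 15%:
- 15% vs 0%: 49%, then 25% and 19%.
- 25% vs 10%: 30%, then 19% and 16%.
- 10% vs 2%: 9%, then 8% and 7% (relative risk 5.0, then 1.61 and 1.41).

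Most of the loss is in precision and in the relative measure; the absolute difference moves little. For an excess of about 8 points, power is below 10% whichever events are counted.

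**The case against.** The protocol never says that events before allocation will be counted by arm. Section 8.1.2 gives only a label, section 2 speaks of the one-year follow-up, and a counting window may sit in an SAP that is not shown. That is fair as far as the window goes. It does not reach the objective and hypothesis, which this document fixes, or the need to record timing during surgery.

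The leakage rate is a weak proxy. It comes from earlier experience, section 9.2.1 expects fewer leaks with the present technique, and it is not said to precede clipping. This stands, and is why q is labelled an assumption.

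Section 10.1 makes any test two-sided, so harm can be detected despite the wording. This also stands: the wording affects interpretation more than the test.

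A reader might infer that closing the clip is the only safety contrast that matters. The documents do not support that. Sections 8.7 and 9.5 rest the safety review and the termination criterion on surgical damage during the operation, without reference to arm. Postoperative leaks, positional vertigo, hearing loss and meningitis can all appear after allocation. Nor is the step after allocation cleanly described as clip closure alone: under section 5.1 the decompression text follows the CT scan, and the EDB text has a fallback for an unidentified duct although randomisation presupposes that it was identified.

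**Conclusion.** The point holds as a cheap improvement of minor to moderate priority. Nearly all the hazardous dissection precedes randomisation, yet complications are set up as a between-arm outcome expected to favour EDB, with no split at allocation.

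In the illustration, counting all events takes power from 36% to 21% or 17% and the relative risk from 4.0 to 1.9 or 1.7, while the risk difference loses 10-15% of its size. This rests on assumed post-allocation risks, independence of the two stages, and 10-15% of patients having an event before allocation.

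Two stronger readings are not supported. One is that pre-allocation events bias the comparison toward an arm: they are balanced in expectation. The other is that they swamp it: the drop from 49% to 25% or 19% requires no post-allocation complications at all in the decompression arm, and for small excesses the trial has little power with or without the change.

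**What to change.** 1. Add an eCRF field, completed before the randomisation call, for intraoperative events already recognised.
2. Compare the arms on events recognised after allocation, including all postoperative events, in all randomised patients. Report a risk difference with a 95% confidence interval. Keeping every randomised patient in the denominator preserves intention to treat.
3. Also report all complications, overall and by arm, as whole-procedure risk for the safety review.
4. In sections 1 and 2, replace the expected benefit for complications with an estimate of excess harm.
5. Reconcile the accounts of what precedes allocation. Section 5.1 places an open clip in everyone before randomisation; its decompression text does not mention that clip and describes decompression after the CT scan; its EDB text covers an unidentified duct. Section 8.2.1 moves from skeletonising the sac to randomisation, and section 8.3.2 describes clip placement as confined to EDB. The field in item 1 needs one agreed sequence.

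The cost is one eCRF field and some wording. Complications that surface only after surgery cannot be assigned to a stage and stay in the comparison, and power remains low, so the confidence interval should carry the interpretation.
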